##### SCL Measurement

SCL will be quantified using the enzyme-linked immunosorbent assay (ELISA) methodology. Sampling will be conducted at 4 distinct time points during the day, namely upon awakening [35], 30 minutes after awakening [36], before sleep (30 minutes before bedtime) [37], and immediately before bedtime [38] (with the timing adjusted to fall within the range of 9 PM to 1 AM, contingent on each participant’s self-selected bedtime). This collection process will be carried out during 3 distinct cycles, namely at baseline, 4 weeks, and 8 weeks.

Saliva samples will be gathered using a Salivette collection system (hygienic saliva collection; Sarstedt) [36] and stored in a –20 °C freezer until they undergo analysis using the General Cortisol ELISA Kit (RK00639; ABclonal) [39]. The participants will be provided with specific instructions not to engage in eating, drinking, toothbrushing, or strenuous physical activity within the 30-minute interval preceding each saliva sampling session.

##### fMRI Examination Procedure

fMRI data will be acquired from all of the participants using a 3.0-T Trio Siemens System (SIEMENS AG) at the Yueyang Hospital of Integrated Traditional Chinese and Western Medicine affiliated with the Shanghai University of Traditional Chinese Medicine, Shanghai, China. A total of 30 participants will be scanned under the following conditions: repetition time=1900 ms; effective echo times=2.93 ms; sagittal slices=188; thickness/skip=1.2/0.6 mm; field of view=256 × 256 mm^2^; matrix=240 × 256 mm^2^; voxel size=1.0 × 1.0 × 1.0; phase encoding direction=A >> P; and flip angle=90°. The participants will be requested to rest for 10 minutes with their eyes closed, and they will be requested not to think about anything before the scan. They will be asked not to move the head during data acquisition. We will acquire 242 3D image volumes with the following parameters: repetition time=2000 ms; effective echo times=30 ms; section thickness=1 mm; sagittal slices=32; field of view=256 × 256 mm^2^; matrix=64 × 64 mm^2^; and flip angle=90°. Both groups of participants will be examined before and after treatment.

### Sample Size

The following 2 hypotheses are related to the differences between the 2 groups:

Hypothesis 1: μ_1_= μ_2_Hypothesis 2: μ_1_≠ μ_2_,

where μ_1_ is the PSQI mean score of the 8-week treatment in the BDJQG group, and μ_2_ is the PSQI mean score of the 8-week treatment in the CBTI group.

The required sample size has been calculated using an estimation formula based on the difference between 2 sample means and SDs (PSQI, which is assessed using composite points of sleep quality). Therefore, in a study with this sample size, the difference between the BDJQG group and the CBTI group will be considered, and the conservative comparison method by Bonferroni will be adopted. In this study, it is expected that the BDJQG group will be 1.78 points better than the CBTI group in the PSQI scale mean score. The final calculated difference and SD of the 2 groups of the PSQI mean scores were calculated [40]. On the basis of 0.9 power to detect a significant difference (α=.025; 1-sided), 34 participants will be required for each group.

The following formula was used to calculate the sample size in this trial:

[figure not shown]

Given that an attrition rate of ~20% is anticipated, our target enrollment will be 43. Therefore, a total of 86 participants should be recruited for this RCT.

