### Outcomes

#### Primary Outcome (PSQI)

The primary outcome is the change in PSQI from baseline to week 8. The PSQI is a comprehensive self-report instrument comprising 19 items aimed at evaluating sleep quality and disturbances experienced within a 1-month time frame. These items collectively contribute to the generation of 7 distinct “component” scores, encompassing assessments of subjective sleep quality, sleep latency, sleep duration, habitual sleep efficiency, sleep disturbances, use of sleeping medication, and daytime dysfunction. The sum of the scores derived from these 7 components yields a singular global score. The total global score spans a range from 0 to 21, with a lower global score indicative of a higher quality of sleep [28].

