### Statistical Analysis

The collected data will meticulously be entered into Microsoft Excel (Microsoft Corporation), and subsequent statistical analysis will be conducted using SPSS software (version 18.0; SPSS Inc). Continuous variables will be summarized using the mean value and SD, with the median and IQR used for variables exhibiting nonnormal distributions. Categorical variables will be presented as frequencies or percentages.

For within-group comparisons, paired 2-tailed *t* tests will be used. Between-group differences will be analyzed through 2-sample, independent-sample *t* tests, with effect sizes computed using Cohen *d* statistics. Furthermore, demographic characteristics, baseline measurements, and changes in measurements from baseline to study completion between the 2 groups will be analyzed using 2-sample, independent-sample *t* tests. In cases where baseline measurements exhibit disparities, analysis of covariance will be implemented to account for these variations when comparing the 2 groups.

The clinical overall efficacy evaluation will be based on a nonparametric test for 2 independent samples. In instances of limited participant numbers within a specific subject or in the presence of missing data, the Mann-Whitney *U* test will be used to assess differences between the groups. A statistical significance level of *P*<.05 will be used, signifying statistical significance when this threshold is met.

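### The hypotheses and 90% power are stated on the PSQI mean score, the declared primary outcome is the change in PSQI, and the analysis section ties the decision to no single PSQI contrast

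*Protocol article*

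**What the plan says.** The Abstract and the Primary Outcome (PSQI) section agree on one primary outcome: "The primary outcome is the change in PSQI from baseline to week 8".

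The Sample Size section sets up equality against inequality of two means. The first, μ1, "is the PSQI mean score of the 8-week treatment in the BDJQG group"; the second, μ2, "is the PSQI mean score of the 8-week treatment in the CBTI group". The effect is on the same variable: "it is expected that the BDJQG group will be 1.78 points better than the CBTI group in the PSQI scale mean score". So is the SD: "The final calculated difference and SD of the 2 groups of the PSQI mean scores were calculated". The result is then given: "On the basis of 0.9 power to detect a significant difference (α=.025; 1-sided), 34 participants will be required for each group". No SD is printed. The section also says that a Bonferroni comparison will be used, but names no set of tests and no divided alpha.

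The Statistical Analysis section first gives a general statement, "Between-group differences will be analyzed through 2-sample" independent-sample t tests, without naming the variable. The next sentence adds that demographics, baseline values and "changes in measurements from baseline to study completion between the 2 groups will be analyzed" by the same kind of test. ANCOVA follows, but only where baseline values differ. One threshold, P<.05, covers everything. Bonferroni is not mentioned there.

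**The concern.** The sample size belongs to a comparison of scores and the declared primary is a comparison of changes. These have different standard errors unless the correlation between baseline and week-8 PSQI takes one particular value. The article gives neither that correlation nor an SD of change, so a reader cannot tell what power the declared primary analysis has.

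The analysis section then leaves room for up to three between-group contrasts on PSQI: scores, changes, and an adjusted comparison triggered by observed baseline differences. They can give different verdicts on the same data. The trial is open-label and its primary outcome is self-reported, so a choice of contrast that is still open at analysis weakens the result even if nobody abuses it.

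**Working it through.** **Inputs from the Sample Size section:** difference 1.78; one-sided alpha .025 (z = 1.960); power 0.90 (z = 1.282); 34 per group; attrition about 20%.

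**Inputs not in the document, so assumed:** the correlation r between baseline and week-8 PSQI, varied from 0.2 to 0.7; and the ratio k of baseline SD to week-8 SD, taken first as 1 and then varied from 0.7 to 1.2.

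**1. The plan's own figure.** No SD is printed, so 34 cannot be checked directly. Solving the usual two-means formula backwards:

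SD = 1.78 / [(1.960 + 1.282) × √(2/34)] ≈ 2.26.

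Any SD from about 2.23 to 2.26 rounds up to 34 per group. The inflation reproduces: 34 / (1 − 0.20) = 42.5, rounded up to 43 per group and 86 in total.

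**2. Power of a change-score t test, equal SDs.** SD of change = 2.26 × √[2(1 − r)]. Power is from the noncentral t with 66 df.

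| r | SD of change | Power, 34 per group |
|---|---|---|
| 0.2 | 2.86 | 71% |
| 0.3 | 2.68 | 77% |
| 0.4 | 2.48 | 83% |
| 0.5 | 2.26 | 89% |
| 0.7 | 1.75 | 98% |

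The 89% at r = 0.5 is the planned 90%. The SD was back-solved with the normal formula, and the t distribution gives 89% for the raw-score test too.

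**3. Unequal SDs.** In general, SD of change = 2.26 × √(1 + k² − 2kr). It equals the week-8 SD when r = k/2, so the break-even is r = 0.5 only if k = 1. At r = 0.3:

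| k | SD of change | Power |
|---|---|---|
| 0.7 | 2.34 | 87% |
| 0.8 | 2.44 | 84% |
| 1.0 | 2.68 | 77% |
| 1.2 | 2.97 | 68% |

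**4. Worst case for the error rate.** Suppose both a week-8 score t test and a change t test were run and a win on either were counted. With equal SDs the two statistics correlate at √[(1 − r)/2]: 0.63 at r = 0.2, 0.50 at r = 0.5, 0.39 at r = 0.7. From the bivariate normal with critical value 1.96, the chance of at least one two-sided rejection under no effect is 8.6%, 9.1% and 9.4%, against 5%. In the favourable direction alone it is 4.3%, 4.5% and 4.7%, against 2.5%. Under the planned effect the two tests would disagree in about 23% of trials at r = 0.2 and 10% at r = 0.7.

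**5. ANCOVA.** Adjusting week-8 PSQI for baseline gives a residual SD of 2.26 × √(1 − r²): 2.22, 1.96 and 1.62 at r = 0.2, 0.5 and 0.7. With 34 per group, power is about 90%, 96% and 99%, ignoring the one degree of freedom spent on the covariate. With baseline in the model, the treatment coefficient is the same whether the response is the week-8 score or the change.

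**The case against.** The strongest reply is that the article does declare one outcome, one scale and one time point, so the change should take precedence. The Statistical Analysis section names neither PSQI nor week 8 in its first t-test sentence. That sentence can be read as the general method and the next one as the list of where it applies. On that reading the only post-baseline t test named is the one on change. This stands in part. A reader might infer that the plan specifies two rival PSQI tests and lets either decide, with an error rate near 9%. The document states no such rule, so that figure is only a worst case. Even so, the section does not tie the decision to the change, and the conditional ANCOVA remains as an alternative.

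A second reply is that the mismatch may be in wording only. The description of the means is loose, the formula is not shown, and the difference and SD come from a cited source that is not at hand. That is possible. But nothing in the Sample Size section makes the quantity a change, and the wording needs correcting on either explanation.

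Third, a reader might infer that the trial is underpowered. The document does not support that. Power for a change score is lower than planned if r is below k/2 and higher if it is above, and neither r nor k is given. The ISI limit of 8 to 21 at entry could also narrow the baseline spread, which lowers the break-even.

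Finally, the Bonferroni sentence might seem to cover multiplicity. It names no family of tests and no adjusted level, so it does not settle which contrast decides. A separate analysis plan may do so, but it would not make the outcome and sample-size sections of this article agree.

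**Conclusion.** The point holds as an inconsistency to be corrected. The declared primary is a change, the hypotheses and power are written on a score, and no single PSQI contrast is tied to the decision. Randomization makes all the contrasts target the same treatment difference, so the estimand is not at issue. What is at issue is an open choice of deciding test and a 90% power not shown to apply to the declared primary.

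If the implied SD of about 2.26 is the week-8 SD and the SDs are equal at both visits, change-score power runs from about 71% to 98% for r from 0.2 to 0.7. At r = 0.3 it runs from 87% down to 68% as the baseline SD goes from 0.7 to 1.2 times the week-8 SD. These ranges rest on assumed r and k. They show that the power is undetermined, not that it is too low.

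**What to change.** In Sample Size, write the hypotheses on the declared primary, the PSQI change from baseline to week 8. Print the SD and the baseline-to-week-8 correlation used, and restate the power of 34 per group for the contrast that will decide.

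In Statistical Analysis, name one week-8 PSQI contrast as the only deciding test. ANCOVA with baseline PSQI as covariate, always applied, is preferable. It replaces the ANCOVA that depends on observed baseline disparities, and it removes the choice between score and change because the treatment effect is the same for both. Label the remaining t tests as supportive. Either attach the Bonferroni statement to a named set of tests or delete it.

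The cost is wording and one recalculation, with no extra participants or data. The article reports 86 participants already, so restating power cannot change the enrolment target, but the deciding test can still be fixed before analysis begins. The downside is that the stated power may become less favourable, particularly if an unadjusted change-score t test is kept as the deciding test.

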### Recruitment

To attain the requisite participant enrollment necessary to achieve our predetermined target sample size, recruitment will be conducted within the Shanghai area. These endeavors will encompass the dissemination of recruitment materials through posters, promotion through WeChat public accounts, engagement with individuals attending outpatient clinics, and outreach to those using medical examination centers.

### Randomization and Blinding

Following a postbaseline assessment, the eligible participants will be randomly allocated to the BDJQG group and the CBTI group, adhering to a 1:1 equal proportion allocation. A randomization list will be meticulously generated by a skilled statistician using a computer program (Strategic Applications Software, version 9.1.3; SAS Institute Inc). The generated random sequences will be sequentially numbered by the statistician, who serves as the architect of the randomization sequence. Subsequently, the sequences will be placed within opaque envelopes by a designated project manager, uninvolved in the recruitment process. These sealed envelopes will ultimately be delivered to the research team.

Before implementing the random assignment procedure, the research team will diligently record the particulars of each participant at the clinical center. These records will encompass the participant’s information, such as name, date of birth, participant and center codes, and the inclusion date. Following a meticulous review of the participant’s information by the research team to ascertain eligibility, a sequence will be randomly drawn from the envelope. The selected sequence will be applied to label the participant’s data, designating the participant’s assignment to one of the study groups. This information will then be conveyed to the respective participants.

It is noteworthy that, due to the specific nature of the intervention approach, this study is an open trial, with only the statistical analysis experts being kept blinded, as delineated in the research conducted by Cheng et al [41].

### Adverse Events and Assessment of Safety

Adverse events (AEs) encompass any untoward and nonsignificant occurrences, namely abnormal experimental findings, symptoms, or illnesses that transpire during the course of the study, irrespective of their causal relation to the intervention. It is important to note that numerous authors have attested to the relative safety of qigong as an approach to addressing various health conditions, including hypertension, with no records of severe AEs. In the event of any unexpected AEs, categorized as functional abnormalities brought about by the intervention, such as symptoms like headache, dizziness, vertigo, head distension, tinnitus, chest tightness, aggravated shortness of breath, heart palpitations, muscular soreness or pain, profuse cold perspiration, irritability, neurasthenia, hallucinations, paranoia, or psychological stress—regardless of their treatment association—prompt notification will be made to the nearest affiliated Shuguang Hospital physician. The physician will then conduct an assessment and initiate appropriate medical intervention.

In instances where serious AEs are encountered, the investigator will promptly report the incident to the primary investigator and the ethics committee to collectively determine whether the affected participant should be withdrawn from the study and the associated treatment. The investigator will earnestly strive to avert and manage any potential harm that may arise during the course of the study. If, following the assessment by the expert committee, the AE is determined to be linked to the qigong treatment, the research team will assume responsibility for covering the cost of treatment and providing appropriate financial compensation for any damage arising from the trial. This comprehensive approach to describing AEs and ensuring the assessment of safety closely adheres to the framework delineated in the study conducted by Guan et al [27].

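### The only adverse event definition is restricted to nonsignificant occurrences and the unexpected-event sentence contradicts itself on cause, so AE counts could be incomplete or inconsistently classified

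*Protocol article*

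**What the plan says.** All the operative wording is in the protocol article, Methods, Adverse Events and Assessment of Safety.

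- **Definition.** AEs are "any untoward and nonsignificant occurrences", further described as "namely abnormal experimental findings, symptoms, or illnesses that transpire during the course of the study", and counted "irrespective of their causal relation to the intervention".
- **Unexpected events.** The section refers to "any unexpected AEs, categorized as functional abnormalities brought about by the intervention", gives a list of examples, and requires a physician to be notified "regardless of their treatment association". The list includes chest tightness, hallucinations and paranoia.
- **Serious events.** These have their own route to the primary investigator and the ethics committee. The section does not say what makes an event serious.
- **Compensation.** If, after an expert committee's assessment, "the AE is determined to be linked to the qigong treatment", the research team pays for treatment and compensates the participant.

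Two other places rely on the AE term. Table 1 schedules AE collection during weeks 1-8, at week 8 and at week 12. The withdrawal criteria in Textbox 1 remove a participant who has an AE attributable to the research, without distinguishing the arms.

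**The concern.** An AE definition decides what is written down. This one attaches a severity condition that points the wrong way: an event has to be nonsignificant to count. Staff who applied it literally would leave out the events that matter most for safety, except those that reach the separate route for serious events.

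The second problem is cause. The definition disregards it, the description of unexpected events requires it, and the end of that same sentence disregards it again. A reader cannot tell whether an unexpected event thought to be unrelated belongs to the class.

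At stake are the completeness and consistency of the AE counts and the application of the withdrawal criterion. According to Randomization and Blinding, the trial is open and only the statistical analysts are blinded. Any judgement that the unclear wording invites would therefore be made by people who know the allocation.

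**Working it through.** No arithmetic applies: the point does not depend on alpha, power, effect size or SD, and the documents give no AE rate. The check is to set the statements side by side.

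**Step 1. Severity.** The definition joins two conditions with *and*: untoward, and nonsignificant. The second word is not defined, so three cases are worth comparing.

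| Case | Minor event | Significant, not serious | Serious event |
|---|---|---|---|
| Literal: nonsignificant means of no importance | AE | outside the definition | outside the definition, but has its own route |
| Charitable: nonsignificant means not serious | AE | AE | outside the definition, but has its own route |
| Word deleted | AE | AE | AE, with its own route |

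In the first two cases a serious AE is not an AE under the definition, although the section uses that term. In the literal case there is also a middle group that no stated class holds. That group is a consequence of the literal reading; the document does not itself use such a category.

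**Step 2. The section's own examples.** Hallucinations, paranoia and chest tightness are listed as AEs. They sit badly with a definition limited to nonsignificant events. The section evidently does not intend the literal reading, but its text states it.

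**Step 3. Cause.** There are three statements on whether cause matters:

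1. Definition: "irrespective of their causal relation to the intervention". It does not matter.
2. Unexpected AEs, description: "categorized as functional abnormalities brought about by the intervention". It does matter.
3. Unexpected AEs, same sentence: "regardless of their treatment association". It does not matter.

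Statements 1 and 3 agree with each other; statement 2 conflicts with both. This defect is separate from step 1. The gap for significant events comes from the word nonsignificant alone, while the conflict on cause leaves it unclear which events belong to the unexpected class.

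**Step 4. Dependent text.** The withdrawal criterion needs two things from this section: what an AE is, and when one counts as related. The first is affected by step 1. On the second, the section speaks of the intervention in one place and of qigong in another, whereas the withdrawal criterion speaks of the research as a whole.

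**Step 5. What is not touched.** Safety is not among the listed primary or secondary outcomes, and the Sample Size and Statistical Analysis sections do not use AE data. The primary comparison on the Pittsburgh Sleep Quality Index, its sample size and its type I error are unaffected.

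**The case against.** The strongest reply is that nonsignificant is a slip of wording or translation. If it means not serious, then the definition and the serious-event route together cover every event. The listed symptoms would still be notified, and the section describes no step at which someone judges significance and discards an event. Most of this stands. The slip is probable, and no lost event is shown. It does not remove the point, because this is the only AE definition in the document, and even the charitable reading leaves serious AEs outside the class they are named after.

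A reader might go further and infer that causality is reviewed in the qigong arm only, because the clause on events found to be linked to treatment names only qigong. The text does not support that. The clause governs treatment cost and compensation. The expert committee's assessment that precedes it is not restricted by arm, and neither Table 1 nor the withdrawal criterion distinguishes the arms. What remains is a difference in wording to be reconciled.

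A reader might also conclude that the safety comparison between the arms would be uninterpretable. That too goes beyond the text: no formal safety comparison is listed as an outcome, and nothing shows how many events, if any, would be affected.

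Finally, the article condenses a fuller protocol (version 1.0, according to Ethical Considerations), which may word this correctly. That would limit the problem to the article. It would not make the published wording right.

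**Conclusion.** The point holds as a wording defect in operative safety text. Read literally, the definition excludes significant events, contrary to the same section's serious AEs and its own examples. The unexpected-event sentence also both requires and disregards a causal link. AE counts, and use of the withdrawal criterion, could therefore be incomplete or inconsistently classified in an open-label trial.

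The size is unknown. It depends on how staff actually read the definition, which the documents do not show. If they recorded every untoward event, the effect on the data is nil and only the text needs correcting. If they applied the word literally, significant events short of serious could be missing from either arm. Efficacy conclusions are not affected on either reading.

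**What to change.** 1. Delete the word nonsignificant, so that an AE is any untoward occurrence during the study irrespective of cause. The rest of the sentence already says this.
2. The Results section reports 86 participants already in the trial and data collection since April 2023. Check the events already recorded against the corrected definition before safety is summarised. State in the report if staff worked to the narrower wording, because events never written down may not be recoverable.
3. Reconcile the two phrases on cause in the unexpected-event sentence with each other, with the definition, and with the withdrawal criterion. Which events trigger notification or withdrawal is a clinical matter for the sponsor and investigators, and no rule is proposed here.
4. Reconcile the compensation clause, which names only qigong, with the arm-neutral wording of the withdrawal criterion.

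The cost is a wording correction in one section, a check of its agreement with Textbox 1, and one pass through the recorded events. No visits or assessments are added.
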